### Relevant concomitant care permitted or prohibited during the trial {11d}

To appropriately evaluate the efficacy of the intervention, concomitant care is restricted during the study period. Participants are permitted to continue their stable usual care, such as prescription medications or physical therapy, provided that the type, dosage, and administration remain unchanged. In contrast, they are asked not to (1) initiate other psychotherapy or participate in other clinical trials; or (2) begin medical examinations or treatments that meet the exclusion criteria, such as interventional pain procedures, medical narcotics, or intravenous infusions for pain relief. If a change in usual care is medically necessary, this takes priority, and the participant is instructed to report the change at the next visit. When participants have an attending physician at another hospital, a written summary of the study requirements is also sent to the physician to request that the participant’s usual care remain unchanged from enrollment until the post-assessment.

### Provisions for post-trial care {30}

CBT-CP in this study is limited to eight sessions and will not continue after trial completion. Thereafter, participants will continue to receive usual care from their attending physicians. In the unlikely event of harm related to trial participation, appropriate medical treatment will be provided within the framework of routine clinical care under the Japanese health insurance system. As this trial involves only minimal risk—CBT-CP is delivered as an adjunct to usual care and is not expected to cause serious adverse events—no financial compensation or additional allowances will be provided. Participants are informed of these provisions in advance and give their consent accordingly.

### Outcomes {12}

#### Primary outcome

The primary outcome is health-related QoL, assessed using the EQ-5D-5L [30]. The Japanese version, which has a reliable and valid Japanese scoring system [31], is used. Scores range from 0 (death) to 1 (full health).

#### Secondary outcomes and psychosocial variables

Secondary outcomes include a range of psychosocial variables, which may serve not only as outcomes responsive to CBT-CP but also as potential mediators or moderators of change in QoL, the primary outcome. These are assessed as follows:Health-related QoL (secondary measure): Mental and physical health-related QoL is assessed using the Medical Outcomes Study 12-Item Short Form Health Survey (SF-12), which yields physical and mental component summary scores [32]. In Japan, the inclusion of a role/social component summary has also been recommended and validated [33]. These components are calculated based on the 2007 national norms, with scores ranging from 0 to 100 [34]. Higher scores indicate better health status.Pain severity: Pain severity is assessed using the numerical rating scale (NRS), with 0 indicating no pain and 10 indicating the worst imaginable pain [35]. Participants rate their pain experienced in the last week as follows: (1) maximum, (2) minimum, (3) average, and (4) current. For analysis, the average score is used to maximize reliability [35, 36]. Higher scores indicate greater pain severity.Disability: Disability due to chronic pain is assessed using the Pain Disability Assessment Scale (PDAS) [37, 38], which evaluates limitations in physical exercise and movement. Its reliability and validity have been reported [37, 38]. Higher scores indicate greater disability.Depressive symptoms: The Patient Health Questionnaire-9 (PHQ-9) is used to assess depressive symptoms common in primary care, according to the Diagnostic and Statistical Manual of Mental Disorders [39]. The Japanese version is reliable and valid [40]. Higher scores indicate poorer mental health.Pain catastrophizing: The Pain Catastrophizing Scale (PCS) is used to assess cognitive factors that sustain chronic pain [41, 42]. The Japanese version is reliable and valid [43], with higher scores indicating greater catastrophizing.Fear of movement: Fear of movement is assessed using the Japanese version of the Tampa Scale for Kinesiophobia 11 (TSK-11), which has sufficient reliability and validity [44]. Higher scores indicate greater fear of movement.Pain self-efficacy: Pain-related self-efficacy is assessed with the Pain Self-Efficacy Questionnaire (PSEQ) [45]. The Japanese version is reliable and valid [46]. Higher scores indicate greater confidence in performing activities despite pain.

In addition, two further variables are included as potential moderators:Prognostic risk: The Keele STarT Back Screening Tool generic condition (STarT Back) [47], which assesses physical and psychosocial prognostic factors for chronic pain. The Japanese version is reliable and valid [48, 49]. Scores classify patients into three prognostic risk levels.Somatic symptom burden: The Somatic Symptom Scale-8 (SSS-8) [50], which assesses the overall burden of somatic symptoms. The Japanese version is reliable and valid [51]. Higher scores indicate greater burden of physical symptoms.

#### Demographic and clinical characteristics

Demographic and clinical characteristics are collected at the initial evaluation using a standardized background checklist. Eligibility criteria are first confirmed and recorded. Data collected include:Demographic information, such as age, sex, education, family structure, and employment status.Clinical information, such as pain site, diagnosis, pain duration, medical history, and current clinical condition.Treatment history and status, such as previous and current pain treatments, medication use, and related healthcare utilization.

#### Process measures

At the start of each visit, physicians, therapists, or a research assistant verbally check for adverse events and any changes in usual care. During the intervention period, at the beginning of each session, participants rate their sense of completeness, average pain intensity, and sense of coping with pain in the last week on an 11-point scale (0–10) by the therapist.

### Participant timeline {13}

The participant timeline is shown in Fig. 1. After providing informed consent, participants undergo an initial evaluation, followed by a baseline assessment within 4 weeks (defined as 0 weeks for the trial schedule). Eligible participants are then enrolled and randomized in a 1:1 ratio to the intervention group (TAU plus CBT-CP) or the waitlist control group (TAU only).

**Fig. 1 Fig1:**
[figure not shown]
CONSORT diagram for this clinical trial. *Abbreviations: CBT-CP* cognitive behavioral therapy for chronic pain, *TAU* treatment as usual. Post- and follow-up assessments are conducted in person at the participating hospital. If participants cannot attend within the assessment window, they may complete a mailed questionnaire or respond by telephone

Randomization is performed centrally using an electronic data capture (EDC) system (HOPE eACReSS; Fujitsu Ltd.), managed by the Translational Medical Center of the National Center of Neurology and Psychiatry. Stratified block randomization is applied by hospital (study site). To emphasize transparency, registration and randomization are usually performed in front of eligible participants on a study computer, unless there is a specific reason not to do so.

Both groups undergo a post-assessment at 15 ± 2 weeks. The intervention group receives CBT-CP with the goal of completing all eight sessions within 14 weeks. If the intervention extends beyond the 15th week, the post-assessment is nevertheless conducted at 15 ± 2 weeks as scheduled. A follow-up assessment at 27 ± 2 weeks is conducted only for the intervention group to explore mid-term effects because the timing of CBT-CP initiation for the waitlist control group depends on post-assessment findings and/or social circumstances, making follow-up assessment impractical. Although collecting follow-up data for the waitlist control group would have been desirable, it was judged unfeasible to obtain consistent data under these circumstances.

All assessments are in principle conducted in person at the participating hospital. However, for the post-assessment and follow-up assessment, if participants are unable to attend within the assessment window (± 2 weeks), they may instead complete a mailed questionnaire or provide responses by telephone.

### Sample size {14}

In the preceding pilot study, among participants with baseline EQ-5D-5L ≤ 0.80 (12 of 15), Hedges’ g for EQ-5D-5L from baseline to post-treatment was − 1.24 (90% confidence interval [CI]: − 2.14 to − 0.34), with the negative sign reflecting model coding (improvement); the corresponding mean difference was 0.18 (90% CI: 0.09 to 0.27) [22]. Because this was a within-participants effect size without a control group, it is treated only as a reference value. For between-participant comparisons of QoL, a meta-analysis reported a CI ranging from − 0.74 to 0.11 for the effect size of CBT-CP [52]. In addition, an RCT in patients with low pain intensity yielded an effect size of 0.23 [53], whereas an RCT in patients with high pain intensity reported an effect size of 1.92 [54], suggesting a dose-response relationship between baseline pain intensity and treatment effect [55].

Based on these findings, we set the anticipated effect size for this trial at 0.74, the upper limit reported in the meta-analysis [52], because this study targets patients with relatively high chronic pain intensity. The dropout rate was assumed to be 20%, and the correlation between time points for the primary outcome was set at 0.50, based on the pilot study [22]. With a two-sided significance level of 0.05 and a statistical power of 0.90, the required sample size for a linear mixed model (LMM) analysis [56] was calculated as 30 participants per group. Accordingly, the target total sample size is 60 participants, with 30 in each arm.

### Recruitment {15}

Participants are primarily recruited from the outpatient clinics of the participating hospitals, where physicians approach potentially eligible patients during routine clinical visits. Those who express interest are then provided with written information about the study. In addition to this direct recruitment, participants may also be referred by colleagues or affiliated institutions, or may contact the hospital themselves after finding information about the study on the study website. To enhance the likelihood of reaching the target sample size, the trial is organized as a multicenter collaboration across seven hospitals in Japan, thereby enabling recruitment from a broader patient base.

At the same time, opportunities to provide CBT-CP in routine practice are still limited in Japan. Clinical care understandably takes priority in everyday hospital settings, and in many departments that treat chronic pain, psychologists are not employed at all, even on a part-time basis. Even when a psychologist is present, they are not necessarily able to deliver CBT-CP, either because their clinical hours are very limited or because their therapeutic orientation is not CBT. In this trial as well, the same constraints apply: CBT-CP is provided mainly by therapists qualified to deliver it—most of whom are university faculty collaborating on the study—and they travel to the participating hospitals to conduct the intervention only when eligible participants have been recruited. Because their primary academic duties remain at their home institutions, their availability is restricted to a small portion of time, typically ranging from a half day to 1 day per week. For these reasons, large-scale advertising or mass recruitment is not feasible, and enrolment is being pursued gradually through clinical encounters and professional referrals.

## Assignment of interventions: allocation

### Sequence generation {16a}

Participants are allocated in a 1:1 ratio to the intervention or waitlist control group. Randomization is performed centrally using an EDC system. To avoid imbalance in group allocation across hospitals, stratified block randomization is used, with the seven participating hospitals (study sites) as stratification factors. Details of block size are concealed to maintain allocation unpredictability.

### Concealment mechanism {16b}

The allocation sequence is embedded within the central EDC system and is inaccessible to all study personnel and participants. Registration and randomization are conducted electronically, ensuring that allocation is not revealed until the point of assignment, thereby maintaining strict concealment of the sequence.

### Implementation {16c}

The randomization sequence is generated automatically by the EDC system. At each hospital, collaborating physicians are responsible for recruiting and registering eligible participants, with assistance from therapists or a research assistant when needed, always under the physician’s supervision. Once registration is completed, the EDC system assigns participants to groups. To emphasize transparency, randomization is usually performed in front of participants using the study computer, unless specific circumstances make this impractical.

## Assignment of interventions: blinding

### Who will be blinded {17a}

Because the intervention involves adding CBT-CP to TAU, masking participants, physicians, therapists, and a research assistant is not feasible. Outcomes are assessed exclusively using self-administered questionnaires; therefore, independent outcome assessors are not required. Data analysts work with de-identified datasets with coded group labels. Because the intervention and waitlist control groups are inherently distinguishable, blinding cannot be maintained; however, the standardized manualized program, structured therapist training, supervision, and fidelity procedures help ensure consistent delivery across groups.

### Procedure for unblinding if needed {17b}

Blinding is not applied in this trial; thus, no unblinding procedures are required. Because the intervention and waitlist control groups are inherently distinguishable, accidental unblinding is not an issue.

## Data collection and management

### Plans for assessment and collection of outcomes {18a}

As shown in Table 2, the primary outcome, secondary outcomes and psychosocial variables, demographic and clinical characteristics, and process measures are assessed. Outcomes and psychosocial variables are self-reported using A4 booklet-format questionnaires. Demographic and clinical characteristics at the initial evaluation, as well as process measures during CBT-CP sessions, are obtained verbally by collaborating physicians, therapists, or a research assistant and recorded on standardized forms.

**Table 2 Tab2:** Schematic diagram for the assessment schedule (SPIRIT Fig. 2013)

Time points	Initial evaluation	Baseline assessment	Intervention period	Post-assessment	Follow-up assessment
Visit	1	2	3–10	11	12
Week	−4–0	0	1–14	15 ± 2	27 ± 2
Demographic and clinical characteristics					
Eligibility criteria	V				
Demographic information	V				
Clinical information	V				
Treatment history and status	V				
Primary outcome					
EQ-5D-5L		S		S	S
Secondary outcomes and psychosocial variables					
SF-12		S		S	S
NRS		S		S	S
PDAS		S		S	S
PHQ-9		S		S	S
PCS		S		S	S
TSK-11		S		S	S
PSEQ		S		S	S
STarT Back		S			
SSS-8		S			
Process measures					
Adverse events		V	V	V	V
Changes in usual care		V	V	V	V
Sense of completeness			V		
Average pain intensity			V		
Sense of coping with pain			V		

*Abbreviations and codes*: *S* self-reported by participant, *V* verbally obtained by a physician, therapist, or research assistant, *EQ-5D-5L* EuroQol five-dimensional questionnaire five-level, *SF-12* Medical Outcomes Study 12-Item Short Form Health Survey, *NRS* numerical rating scale, *PDAS* Pain Disability Assessment Scale, *PHQ-9* Patient Health Questionnaire-9, *PCS* Pain Catastrophizing Scale, *TSK-11* Tampa Scale for Kinesiophobia 11, *PSEQ* Pain Self-Efficacy Questionnaire, *STarT Back* Keele STarT Back Screening Tool generic condition, *SSS-8* Somatic Symptom Scale-8

To ensure data quality, all questionnaires are compiled into a booklet that participants complete independently. After completion, collaborating physicians or therapists check for missing responses. Data are then entered item by item into the predefined format of the EDC system, which ensures that any missing responses are identified again during entry. In addition, the system includes range checks to prevent invalid values and automatically calculates scale scores, further reducing the risk of human error. Data entry personnel are also instructed to recheck entries after a time interval to minimize input errors. For verbally collected data, the use of standardized forms and subsequent entry into the EDC system similarly ensures that any omissions are identified at the time of data entry. Because these procedures are straightforward and standardized, no additional training workshop is considered necessary.

Because participants in both the intervention group and the waitlist control group are recruited within the same hospitals, performance bias due to differential expectations of treating physicians cannot be entirely excluded. However, therapists only meet participants when delivering CBT-CP, minimizing the risk of therapist-related bias, and participants in the waitlist control group receive CBT-CP only after the post-assessment, preventing differential treatment during the assessment period. In addition, attending physicians at other hospitals are asked to keep TAU unchanged until the post-assessment. Further measures to reduce bias include the use of a manualized intervention program, structured therapist training and supervision, and treatment fidelity procedures, which are detailed in Items 10, 11a, 11c, and 11d.

### Plans to promote participant retention and complete follow-up {18b}

To promote retention, session schedules (timing and rescheduling) are arranged flexibly, and CBT-CP is provided face-to-face under ordinary circumstances. However, when sessions cannot be held in person owing to regulations by the government, local governments, or implementing institutions, online implementation is also permitted under predefined safety requirements (see Item 11a). Similarly, for the post-assessment and follow-up assessment, if participants are unable to attend within the assessment window, they may complete a mailed questionnaire or provide responses by telephone (see Item 13). Therapists also encourage engagement by reviewing and adjusting homework as appropriate, thereby supporting adherence throughout the intervention.

For participants who discontinue or withdraw from the study, outcome data are still collected at post-assessment, and at follow-up for the intervention group, whenever possible. All available data are included in the analysis according to the intent-to-treat (ITT) principle.

### Data management {19}

Participants’ data are anonymized at each hospital and entered into the EDC system using research IDs, with personal identifiers removed. Paper-based materials such as consent forms, demographic checklists, and completed questionnaires, as well as electronic audio files for supervision, are securely stored in locked cabinets or password-protected drives within each hospital. All such materials are destroyed in an unidentifiable form 5 years after study completion or 3 years after publication, whichever is later. Data management is conducted with careful attention to transparency and future reusability, with anonymized datasets made available for secondary analyses upon appropriate request and following approval by the relevant ethics committee.

### Confidentiality {27}

Research data are coded with research IDs, and linkage to personal identifiers is kept only within each hospital under restricted access. Identifiable information is never shared outside the hospitals. When electronic audio files are temporarily transferred for supervision, a secure, access-restricted online platform is used, and files are promptly deleted after transfer.

### Plans for collection, laboratory evaluation, and storage of biological specimens for genetic or molecular analysis in this trial/future use {33}

No biological specimens are collected in this trial.

## Statistical methods

### Statistical methods for primary and secondary outcomes {20a}

A detailed statistical analysis plan (SAP) will be developed and finalized prior to database lock.

The main analysis will estimate the effect size for the primary outcome (EQ-5D-5L) using LMM [64] based on the ITT principle. The LMM method is selected because of its strength in handling missing data and its ability to incorporate random effects. The analyses will be conducted with the outcome scores at each assessment time point as the dependent variable, time (baseline and post-assessment), group (intervention vs. waitlist control), and interaction between time and group as fixed effects, and participants as random effects. No special treatment will be applied to discontinued cases or missing values for ITT analysis, but as a sensitivity analysis, best- and worst-case scenarios will be examined by imputing hypothetical maximum and minimum plausible values based on the ranges of each scale, defined a priori and prespecified in the SAP. To address the potential non-normality and ceiling effects of the EQ-5D-5L, alternative modeling approaches (e.g., generalized linear models, beta regression) will also be considered in the SAP. Two-sided *p* values < 0.05 will be considered statistically significant.

Secondary analyses will estimate effect sizes for multiple psychosocial outcomes using the same LMM framework. In addition, the intervention group will undergo a follow-up assessment at 27 ± 2 weeks after randomization, and the mid-term effect of CBT-CP will be explored in a single-arm, pre/post comparison. Because multiple secondary outcomes (approximately 11 variables) will be analyzed, type I error will be controlled using Bonferroni correction. However, given the limited sample size, this conservative adjustment is expected to markedly reduce statistical power. Therefore, unadjusted results will be reported as the primary descriptive findings, while results with Bonferroni correction will also be presented to indicate the potential risk of type I error. Effect sizes and CI will be reported to aid interpretation, and all analyses of secondary outcomes will be considered exploratory and primarily hypothesis-generating.

Exploratory analyses will examine whether psychosocial variables, participant characteristics, and process measures function as potential moderators or mediators of treatment effects.

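### The primary mixed model leaves the baseline means free by arm, so it estimates a difference in change and gives up precision that the pre-randomisation baseline could supply

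*Protocol article*

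**What the plan says.** The model is in the Protocol article, Statistical methods for primary and secondary outcomes {20a}. Baseline belongs to the outcome vector and is not a covariate: "The analyses will be conducted with the outcome scores at each assessment time point as the dependent variable". The remaining terms are "time (baseline and post-assessment), group (intervention vs. waitlist control), and interaction between time and group as fixed effects, and participants as random effects". The same framework is used for the secondary outcomes.

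Participant timeline {13} places the baseline assessment before enrolment and randomisation. No section constrains the arms to a common baseline mean or adjusts for baseline. Section {20a} leaves to the SAP the best- and worst-case values and the alternative models for non-normality and ceiling effects. It does not leave the core model open.

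Sample size {14} gives the planning values. On correlation, "the correlation between time points for the primary outcome was set at 0.50, based on the pilot study". On effect size, "we set the anticipated effect size for this trial at 0.74, the upper limit reported in the meta-analysis". Dropout is assumed to be 20%. The stated result is that "the target total sample size is 60 participants, with 30 in each arm".

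Sections {18b} and {20c} keep all available data in the mixed model, without imputation for the primary analysis.

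**The concern.** With one baseline and one post value per participant and a free group main effect, only the interaction measures the treatment effect at the post-assessment. It equals the between-arm difference in mean change. Subtracting the whole baseline difference is more correction than a correlation of 0.50 calls for, and it adds noise to the estimate. A model that uses the fact that randomisation makes the expected baseline means equal removes this noise.

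What is at stake is power in a trial of 60 participants, with an effect size taken from the favourable end of a meta-analytic interval. The lost precision can be recovered from questionnaires that are collected anyway. The same loss carries over to the secondary outcomes, for which the Discussion already calls power limited.

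**Working it through.** **Inputs.** From Sample size {14}: r = 0.50, effect d = 0.74 in post-SD units, two-sided alpha 0.05, power 0.90, dropout 20%, 30 per arm. With 20% of post scores missing, each arm has 30 baseline and 24 post values. The documents give no SDs, so the baseline/post SD ratio k is an assumption and is varied. The post SD is set to 1.

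**The plan's own sample size.** Formula: n per arm = 2v(1.960 + 1.282)²/0.74².
- Difference in change, v = 2(1 − r) = 1.00: n = 38.4, so 39, and 39/0.8 = 48.75, so 49 after dropout.
- Baseline-adjusted, v = 1 − r² = 0.75: n = 28.8, so 29, and 29/0.8 = 36.25, so 37 after dropout.

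The stated 30 per arm is not reproduced for the planned contrast. At two-sided 0.05 and 90% power, it is approached only with v = 0.75 and no dropout allowance. That is a separate matter, but it shows which variance the trial would need.

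**Complete data, equal SDs (k = 1).**
- Planned interaction: variance = 2 × 2(1 − r)/30 = 2/30 = 0.0667, SE 0.258.
- Constrained or adjusted: variance = 2(1 − r²)/30 = 1.5/30 = 0.0500, SE 0.224.
- Ratio = (1 − r²)/[2(1 − r)] = (1 + r)/2 = 0.75, a 25% lower variance.

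Generalised least squares information matrices for the two models give the same ratio. A simulation of 20,000 trials that estimates the ANCOVA slope gives a ratio of 0.776, about 22% lower, so estimating the slope costs a little of the gain.

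**20% of post scores missing, all available data kept, k = 1.**
- Planned: variance per arm = (1 − r²)/24 + (1 − r)²/30 = 0.03125 + 0.00833 = 0.03958. Doubled: 0.0792.
- Constrained: variance per arm = 0.75/24 = 0.03125. Doubled: 0.0625.
- Ratio = 0.789, about 21% lower.

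**Power at d = 0.74, k = 1, normal approximation.**
- Complete data: 81.7% planned, 91.1% constrained.
- 20% missing: 0.74/√0.0792 = 2.63, giving 74.9%; 0.74/√0.0625 = 2.96, giving 84.1%.
- With t reference distributions, the 20%-missing figures are about 73% and 83%.

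**Unequal SDs, r = 0.50 among enrolled participants.** The planned variance per arm is [0.75 + (k − 0.5)²]/30 with complete data and 0.75/24 + (k − 0.5)²/30 with 20% missing. The constrained values are 0.75/30 and 0.75/24.

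| Baseline/post SD ratio k | Variance reduction, complete | Variance reduction, 20% missing |
|---|---|---|
| 1.0 | 25% | 21% |
| 0.9 | 18% | 15% |
| 0.8 | 11% | 9% |
| 0.7 | 5% | 4% |
| 0.5 | 0% | 0% |

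A ratio near 0.8 is plausible. In the pilot, 12 of 15 participants were at or below 0.80. Removing the top 20% of a normal baseline leaves a variance of 0.583. If 0.50 is the correlation before truncation, the post variance is 0.25 × 0.583 + 0.75 = 0.896, and k = √(0.583/0.896) = 0.81. On that reading the correlation among enrolled participants is below 0.50, and the complete-data reduction is 1 − 0.75/0.896 = 16%.

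**The case against.** The strongest reply is that nothing is misstated. Time, group and their interaction with a participant effect form a standard, coherent model that is unbiased under randomisation. This stands: the point concerns efficiency. A reader might infer that the planned test is biased through regression to the mean. The documents do not support that, since the over-correction exists only conditionally on a chance baseline imbalance.

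Second, the 25% needs equal SDs and complete data, while the entry cap acts on baseline only. This also stands, which is why the size is given as a range. A reader might also compare only the 24 completers per arm, where the t-based power is about 71% versus 83%. Sections {18b} and {20c} keep baseline-only participants in the model, so the 73–75% versus 83–84% comparison is the relevant one.

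Third, a reader might back-calculate a lower correlation from the pilot's g, mean difference and interval, and claim a larger loss. That rests on an unstated standardiser for g and on rounded limits, and it overrides the 0.50 that the plan itself attributes to the pilot. It should not be used.

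Fourth, a reader might fault the participant-only random effect for forcing equal variances. With two time points and complete data, the interaction estimate and its SE equal those of the change-score comparison even when variances differ. That complaint matters only through missing post values, and covariance structure is ordinary SAP detail.

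Finally, {20a} does not name the tested term. The interaction is inferred, but with free baseline means no other term measures the effect at post-assessment.

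**Conclusion.** The point holds as a loss of efficiency. The protocol fixes a model that ignores the equality of baseline means created by randomisation. At r = 0.50 and equal SDs, the attainable variance is 25% lower with complete data and about 21% lower with 20% missing post scores. The latter is worth roughly 9 to 10 percentage points of power at d = 0.74. If the entry cap reduces the baseline SD, the variance reduction is about 9–11% at an SD ratio of 0.8 and 4–5% at 0.7. With the covariance known, the constrained model is never less precise than the planned one. The documents give no SDs, so where in this range the trial falls cannot be settled from them. The change is worth making, but validity does not depend on it.

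**What to change.** Before any outcome data are viewed by arm, make the primary model a constrained longitudinal model: fixed effects for time and time-by-group, no group main effect, and an unstructured 2×2 covariance within participant. Name the group contrast at the post-assessment as the primary estimate. This keeps the likelihood-based handling of missing data. ANCOVA of the 15-week EQ-5D-5L on baseline is an acceptable alternative. Use the same form for the secondary outcomes and report the current interaction model as a sensitivity analysis.

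The cost is a wording change in the protocol and SAP. If it counts as an important amendment, section {25} requires ethics approval and a registry update. No new data are needed. The change does not by itself restore the stated 90% power: with 20% dropout, power is about 83–84% at the plan's own effect size, so the sample-size calculation needs separate attention.
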